#### Formative research

Qualitative, in-depth research will be undertaken to understand existing caregiving behaviours, identify individual, household, service, social and environmental determinants of caregiving behaviours (barriers and motivations), and inform the design of the SBC intervention. This will include multi-day immersion by Save the Children trained staff in communities, living with families and informal conversations, observation, and participation in daily household activities, followed by co-creation workshops with communities. Qualitative data will be translated, transcribed, and thematically coded using a set of predetermined codes based on the research objectives and the PIP framework. Codes will then be organised according to common emergent themes and framework matrices will be used for thematic and explanatory analysis.

### Observational studies of other outcomes

A number of observational studies on nutrition, disability, poverty, and developmental dynamics will be conducted in the framework of the cRCT, including a validation study of the Global Diet Quality Score as a proxy for nutrient intake in women, cost of diet, and cohort studies that will include the randomised interventions as covariates in the analysis.

### Economic evaluation

We will estimate the financial and economic costs of the interventions and combine economic costs with measures of impact to estimate the incremental cost-effectiveness ratio (ICER) of the intervention compared to the status quo (the standard of care). The ICER is defined as the incremental cost per outcome gained. We will apply a standardised framework for understanding the costs and benefits of multisectoral nutrition strategies that build on best practices in conducting cost, cost-effectiveness, and benefit–cost analyses [34, 35]. For cost data collection, we will capture all costs incurred by implementing partners, for both inputs (personnel, capital equipment, supplies, overhead) and activities (start-up and disaggregated recurrent activities). We will use a mixed methods approach that combines using financial expense reports obtained by project records, and micro-costing for all resources used that are not captured in the financial analysis. We will capture information on time use by project staff using interview and focus group discussion. Similarly, we will collect time use data and out-of-pocket expenses for volunteers and project participants. We will combine financial and economic costs to estimate the cost per participant using an Excel-based costing model. We will use standard cost-effectiveness methods to estimate incremental costs with net benefits. See Fig. 2 for schedule of enrolment and intervention assessment (SPIRIT Figure).

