**Methods:**

We designed a 3-year cluster-randomised controlled trial in two districts of Malawi, including 156 communities randomised to one of four treatment arms: (1) standard of care (SoC) arm: receiving the standard Government SBC program; (2) SBC arm: receiving the SoC intervention with additional nutrition-sensitive SBC activities to improve nutritious food production, diets, and care practices for young children; (3) low CT arm: SoC plus SBC plus a maternal and child cash transfer ~ 17 USD per month; and (4) high CT arm: SoC plus SBC plus a maternal and child CT ~ 43 USD per month. The trial will enrol pregnant women and children < 2 years of age. The primary outcomes are maternal diet assessed using the mean probability of adequacy and child development assessed using the Malawi Developmental Assessment Tool. Intermediate outcomes along the programme impact pathways will also be measured, including maternal mental health, maternal empowerment, child feeding practices, and child nutritional status.

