1. To examine the effects of the randomised interventions on the Global Diet Quality Score in women 15–49 years of age at baseline who are pregnant or mothers of children 0–2 years of age 2. To examine the effects of the randomised interventions on the adequacy of nutrient intake in children in utero to 2 years of age at baseline 3. To examine the effects of the randomised interventions on height, height-for-age Z-score (HAZ), stunting (HAZ < − 2), weight, weigh-for-height Z-score (WHZ), wasting (WHZ < − 2), mid-upper arm circumference (MUAC), and head circumference in children in utero to 2 years of age at baseline 4. To examine the differential effects of the randomised interventions in the following pre-specified subgroups: a. Female and male children b. Intervention exposure timing/duration (pre-natal/post-natal) c. Subgroups formed by categorising household wealth, food security status, and maternal empowerment 5. To examine effects along the programme impact pathways (PIPs) linking programme implementation of each randomised intervention to nutrient adequacy of intake in women 15–49 years of age at baseline who are pregnant or mothers of children 0–2 years of age and children in utero to 2 years of age at baseline, and other outcomes by assessing: a. Fidelity of intervention implementation for each of the randomised interventions, defined as conformance with implementation specifications b. Quality of community-based childcare centres (CBCC) and care group training and supervision c. CBCC and care group volunteer capacity and service provision as related to the “All Children Surviving and Thriving” framework as assessed by questionnaire and observations d. Attained maternal knowledge and practices as related to the “All Children Surviving and Thriving” framework as assessed by questionnaire and observations 6. To examine the differential effects of the randomised interventions on women’s empowerment and maternal depressive symptoms, and how changes in these indicators mediate the effects on child-level nutrition and developmental outcomes 7. To examine the differential effects of the randomised interventions on household expenditure levels, shares of expenditures, poverty, and food-insecurity levels 8. To examine the differential effects of the randomised interventions on household food consumption elasticities for calories and micronutrients, what factors affect the consumption elasticities, and how changes in elasticities mediate the effects on child-level outcomes 9. To examine the differential effects of the randomised interventions on pregnant women and mothers of young infants’ willingness to pay (WTP) for nutrient-dense complementary foods, what factors affect the WTP for nutrient-dense complementary foods, and how changes in WTP mediate the effects on child-level outcomes 10. To assess costs and incremental cost-effectiveness of the randomised interventions compared to the standard of care 11. To examine the effects of the randomised interventions on haemoglobin concentration and anaemia prevalence in women 15–49 years of age at baseline who are pregnant or mothers of children 0–2 years of age and children in utero to 2 years of age at baseline (conditional on additional funding for data collection)

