#### Cash transfers

The maternal and child cash transfer (CT) intervention contributes to Malawi’s National Social Support Policy of 2012 and the second Malawi National Social Support Programme (NSSP 2017–2022), by expanding CT beyond a poverty reduction-only goal to target pregnant women and mothers of young children. Enrolled women will receive one of two levels of monthly CT for the 3-year duration of the study. The CT will be provided through a mobile phone linked to a bank account registered with each trial participant. Upon registration, participants will be provided with a free mobile phone. The two CT values will be at ~ 17 USD per woman per month and ~ 43 USD per woman per month. The CT values were set based on an analysis of household consumption, poverty, and cost of diet in Malawi. Mean per capita consumption in rural Malawi was estimated at MWK 185,418 (~ 250 USD) [median MWK 151,157 (~ 200 USD)], per person per year, and the national poverty line in Malawi was set at 455 MWK (~ 0.6 USD) per person per day in 2020.^2^ Assuming an average household size of 4.4 members in Malawi, the proposed CT values are equivalent to 0.22 and 0.38 of the estimated monthly household expenditure. Both CT values are higher than the 0.2 rule of thumb threshold from cross-country analysis of the effectiveness of CT interventions [25]. A recent cost of diet analysis in Malawi found a lower bound cost of 1.75 USD (2011 US$ PPP) and upper bound cost of 2.26 USD per person per day [26]. This analysis also found that adequate diets were unaffordable to a minimum of 44% of the population in rural Malawi [26]. Thus, the smaller CT amount of ~ 17 USD per month will help fill the affordability gap for the mother and child’s nutritional needs, whereas the larger CT amount of 43 USD per month will help fill 50% of the affordability gap for the household nutritional needs. Following the completion of the randomised trial, the communities in the standard of care and SBC arms will also receive a one-off CT.

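### The ICER is planned against standard of care alone, although the four arms are nested packages whose cash steps need their own incremental ratios

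*Protocol article*

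**What the plan says.** Two places in the protocol article set the cost-effectiveness comparison, and they agree. Secondary objective 10 (Table 1) reads "To assess costs and incremental cost-effectiveness of the randomised interventions compared to the standard of care". The Economic evaluation section sets out "to estimate the incremental cost-effectiveness ratio (ICER) of the intervention compared to the status quo (the standard of care" and adds: "The ICER is defined as the incremental cost per outcome gained". It also says, in general terms, "We will use standard cost-effectiveness methods to estimate incremental costs with net benefits", and refers to a standardised framework built on best practice. It states no willingness-to-pay threshold and no cost-effectiveness comparison between active arms.

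The design is described in the abstract as "including 156 communities randomised to one of four treatment arms". The packages are nested: "low CT arm: SoC plus SBC plus a maternal and child cash transfer" and "high CT arm: SoC plus SBC plus a maternal and child CT". Table 2 shows the same structure, with 39 clusters per arm. On the amounts, the Cash transfers section says "The two CT values will be at ~ 17 USD per woman per month and ~ 43 USD per woman per month", paid for the 3 years of the study.

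**The concern.** Only one of the four packages can be adopted in a given community, and each contains the one before it. For options of this kind, the ratio that informs a choice compares each package with the next less costly one that is not dominated. A ratio of high cash against SoC mixes three increments: SBC over SoC, low cash over SBC, and high cash over low cash. If SBC is cheap per unit gained, its gain is credited to the cash arms and makes them look better value than the cash itself is.

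The protocol's own aims make this matter. The last paragraph of the Background says that the trial will test the cost-effectiveness of alternative additions to the government programme. The abstract's Discussion stresses synergy between SBC and cash and says that the findings will inform national programmes. Two cash levels were randomised. Whether cash is worth adding to SBC, and whether the larger amount is worth its extra cost, are questions that a ratio against SoC does not answer directly.

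**Working it through.** The protocol states no ICER, so there is no figure of its own to reproduce. The check has an algebraic part and an illustration.

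**Inputs from the protocol**
- Transfers of about 17 and 43 USD per woman per month for 36 months (Cash transfers).
- An SBC effect of 0.23 SD on child development in an earlier Malawian trial (Sample size and power), used only as a reference value.

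**Assumptions (not in the protocol)**
- SBC cost per woman, the same in all three active arms.
- The other effects against SoC.
- The full transfer counts as cost, undiscounted and without delivery cost.

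**Transfer cost per woman**
- Low: 17 × 36 = 612 USD.
- High: 43 × 36 = 1548 USD.
- Low-to-high step: 1548 − 612 = 936 USD.

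**Formulas.** Let C and E be cost and effect relative to SoC.
- Against SoC: C_k / E_k.
- Step: (C_k − C_(k−1)) / (E_k − E_(k−1)).

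The ratio against SoC is the effect-weighted mean of the step ratios. If the steps become more costly per unit, that mean lies below the last step. This does not depend on the numbers chosen.

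**Main illustration.** SBC cost 100 USD; effects 0.23, 0.35 and 0.40 SD.
- Against SoC: 100/0.23 = 435; 712/0.35 = 2034; 1648/0.40 = 4120 USD per SD.
- Low cash over SBC: 612/0.12 = 5100.
- High over low cash: 936/0.05 = 18720.
- Check of the averaging: (0.23 × 435 + 0.12 × 5100 + 0.05 × 18720)/0.40 = 1648/0.40 = 4120.
- Gap for high cash: 18720/4120 = 4.5-fold.

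**Sensitivity to the assumed effects (USD per SD).** The relevant ratio for high cash is its ratio to the next arm on the frontier. Where low cash is extendedly dominated, that arm is SBC.

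| SBC cost | Effects (SBC, low, high) | High vs SoC | Low vs SBC | High vs low | Relevant ratio for high | Gap |
|---|---|---|---|---|---|---|
| 100 | 0.23, 0.35, 0.40 | 4120 | 5100 | 18720 | 18720 | 4.5 |
| 100 | 0.23, 0.40, 0.42 | 3924 | 3600 | 46800 | 46800 | 11.9 |
| 100 | 0.10, 0.30, 0.40 | 4120 | 3060 | 9360 | 9360 | 2.3 |
| 100 | 0.23, 0.30, 0.45 | 3662 | 8743 | 6240 | 1548/0.22 = 7036 (vs SBC) | 1.9 |
| 100 | 0.23, 0.25, 0.30 | 5493 | 30600 | 18720 | 1548/0.07 = 22114 (vs SBC) | 4.0 |
| 180 | 0.20, 0.30, 0.453 | 3815 | 6120 | 6120 | 6120 | 1.6 |
| 180 | 0.20, 0.25, 0.40 | 4320 | 12240 | 6240 | 1548/0.20 = 7740 (vs SBC) | 1.8 |

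In the sixth row the effect of cash is proportional to its amount: 0.20 + 0.10 × 43/17 = 0.453. The SBC cost of 180 USD is 5 USD per month × 36. For the first five effect sets, varying SBC cost from 50 to 200 USD keeps high cash against SoC between about 3600 and 5800. The step ratios do not move, because the SBC cost cancels.

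**The case against.** The strongest reply is that naming SoC as the reference does not forbid comparisons between active arms. The same section commits to standard methods and net benefits. Net benefit is additive: high against SoC minus low against SoC equals high against low, so arm-level net benefits would rank the packages at a given threshold. The section also plans cost per participant, and the Statistical analysis section fits a dummy for each intervention, so step point estimates follow by subtraction. Dominance rules and uncertainty methods are details that an article may leave to a fuller plan. The contrast with SoC also answers a real question, since the primary objective concerns the combined effect of SBC with each cash level.

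Much of this stands. A reader might infer that the plan conceals the value of cash or rules out the step comparisons. The document does not support that, because the point estimates are recoverable if arm-level costs and effects are reported. Nor is the ratio against SoC wrong in itself.

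What does not stand is that the general wording settles the matter. It gives no threshold and no between-arm comparison, whereas the comparator is stated explicitly, twice, once in an objective. Uncertainty for a step cannot be rebuilt from separate intervals against SoC, because those contrasts share the SoC arm and because costs and effects are correlated. The point therefore concerns a stated choice and not missing detail.

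**Conclusion.** The concern holds in a limited form. SoC is the only comparator named for the ICER. For nested packages with diminishing returns, a ratio against SoC understates the cost per unit of effect of the cash steps, and the plan as written assesses neither the uncertainty of those steps nor dominance.

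The 36-month transfer costs (612, 1548 and a step of 936 USD) follow from the protocol. Everything expressed per SD rests on assumed effects and SBC costs. In the main illustration the gap for high cash is 4.5-fold. Across the seven sets shown it runs from 1.6- to 11.9-fold. Where the effect of cash does not diminish it can be as small as 1.6- to 1.8-fold, although it stays large if cash as a whole adds little to SBC. A reader might take any one multiple as the size of the distortion; the document gives no effects or SBC costs that would support one. The absolute figures also depend on counting the whole transfer as cost. The Economic evaluation section distinguishes financial from economic costs and does not say how transfers are treated.

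This affects a secondary objective and the policy reading of the trial. Randomisation, data collection and the primary outcomes are untouched. It should be changed before the economic analysis is run.

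**What to change.** In the Economic evaluation section and in secondary objective 10, add three statements:
- The four arms will be ranked by cost, and dominated and extendedly dominated arms removed.
- Each remaining arm will be compared with the next less costly non-dominated arm. If none is removed and costs rise in the nested order, these comparisons are SBC against SoC, SBC plus low cash against SBC, and SBC plus high cash against SBC plus low cash.
- Uncertainty will come from the joint distribution of costs and effects, respecting the clustering.

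Keep the ICERs against SoC alongside, since they answer the question about each whole package. It would help to say in the same place how the transfer itself enters financial and economic cost, because the cash steps depend on it.

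The cost is a little more analysis of data already due to be collected. Uncertainty will be wider around the step ratios than around those against SoC, because the differences in effect between adjacent arms are likely to be smaller. That should be reported as it is.

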**Fig. 2 Fig2:**
[figure not shown]
Schedule of enrollment, interventions, and assessments (SPIRIT Figure)

### Data flow and management

All data will be collected using tablets preloaded with questionnaires programmed using CAPI software (Survey CTO). Data collection will include creating anonymised versions of the datasets. The data files in Stata format containing identifying information from the baseline survey will be held only on the principal investigators’ (PIs) computer, for use in tracking and identifying baseline survey respondents during the follow-up surveys. The data will be processed, cleaned, and documented by research assistants working under close guidance of the Pis. The documentation will include questionnaires, data variable labels, value labels, and a codebook to assist in the analysis. Field notes from the fieldwork coordinator and team leaders describing the data collection process will also be stored. Within 12 months of the end of the project, the anonymised data will be made publicly available on the IFPRI website. Users of the data will be asked to provide information on how the data are expected to be used to help IFPRI track the use of the data for research purposes.

### Data monitoring

Adverse events (AEs), serious adverse events (SAEs), or harms from the interventions are not anticipated. There is no anticipated harm and compensation for trial participation. Minor AEs or harms may include community disagreements related to some community members receiving the interventions and others not receiving them. Data on such events will be collected at follow-up surveys. In addition, we will collect data on SAEs in pregnant women (e.g. miscarriage, stillbirth) and children (e.g. child death, severe morbidity) at follow-up surveys to assess any potential negative unintended consequences of the interventions. Interim analyses based on programme monitoring and midline evaluation, including potential unintended effects, will be presented to the trial steering group within 3 months of the midline survey completion. The trial steering group will sign off the study design, interim, and final analyses.

### Statistical analysis

The randomised design allows for the identification of causal impacts of the interventions using comparisons of mean outcomes between the randomised intervention arms at endline. The analysis will follow the intention-to-treat approach, using econometric analysis to control for differences at baseline across intervention arms for all variables of interest. Following Bruhn and McKenzie [36], impact will be assessed using a single difference analysis of covariance (ANCOVA) model with the following form:$${Y}_{i1}={\beta }_{0}+{\beta }_{1}{T}_{i}+{{\beta }_{2}Y}_{i0}+{\varepsilon }_{i}$$where $${Y}_{i0}$$ is the outcome variable at baseline, $${Y}_{i1}$$ is the outcome variable at endline, and $${T}_{i}$$ is a dummy variable for treatment status. The ANCOVA estimator has been shown to provide more efficient estimates of programme impact than difference-in-difference models when auto-correlation of outcomes is low [36]. To account for the cRCT design and the level of clustering of the outcome under analysis, we will employ multi-level regression models [37]. The multi-level models will use both fixed effects with dummy variables for each intervention and random effects at the cluster level (unit of randomisation) to account for clustering and to estimate the standard error in an unbiased manner. Alternative fixed effect models with standard errors clustered at the cluster level will also be considered. Primary analyses will be unadjusted for baseline covariates. In addition, we will report adjusted estimates, controlling for baseline covariates. We will also adjust for the study district to account for any agro-ecological differences that may influence the food security and livelihood interventions. The purpose of the adjustment is to account for imbalances at baseline and to reduce variance. The intent-to-treat analysis strategy will include attempts to follow up all individuals in the study, the development of a main analysis that is valid under a stated plausible assumption on missing data, and sensitivity analysis to explore the effects of departures from the assumption underlying the main analysis. Data management, data cleaning, and statistical analyses will be conducted using Stata, SAS, and R. Results will be reported following the guidelines established in the CONSORT guidance for cRCTs [38].

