## Methods

### Study objectives

The Maziko trial is aimed at evaluating the effectiveness and cost-effectiveness of using the integrated CBCC and parenting care-group platform to improve maternal and child nutrition and development by providing variations of nutrition-sensitive intervention packages in communities receiving standard Government support. The trial addresses one primary objective and several secondary objectives (Table 1).

**Table 1 Tab1:** Objectives of the Maziko trial

Primary objective
To determine the independent effect of nutrition social behaviour change (SBC) and combined effects of nutrition SBC integrated with one of two levels of cash transfers on the adequacy of nutrient intake in women 15–49 years of age at baseline who are pregnant or mothers of children 0–2 years of age at baseline, and on child development (motor, language, and cognition) in children (in utero to 2 years of age at baseline), over a 3-year implementation period
Secondary objectives

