### Sample size and power

The primary outcomes of the trial include women’s diet assessed using the mean probability of adequacy (MPA) of micronutrient intake and child development (motor, language, and cognitive) assessed using the Malawi Developmental Assessment Tool (MDAT). Power calculations based on available clusters in targeted districts and resource availability suggested ~ 40 clusters per intervention arm and 20 households (mother–child pairs) per cluster. Calculations based on MPA and a cRCT design (inter-cluster correlation coefficient (ICC) = 0.05) suggested a Minimum Detectable Effect Size (MDES) of 0.31 SDs. For reference, the effect of the nutrition SBC intervention found during NEEP-IE trial on MPA of children 3–6 years old was 0.34 SDs [27]. Similar calculations for MDAT *Z*-score suggested an MDES of 0.26 SDs (ICC = 0.02). The effect of the SBC intervention on children 6–24 months of age found after a 2-year period (with only 1 year with intervention) during the NEEP-IE trial was 0.23 SDs.

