### Recruitment of subjects

Prior to the baseline survey, a household census was conducted in the CBCC catchment areas which collected information on household demographics and self-reported pregnancy status. Data from the census were used to construct a listing of households for the survey sample with women aged 15–49 years who self-report as pregnant and/or were mothers of children 0–2 years of age. An index dyad (a woman who is pregnant or a mother with a child aged 0–2 years and her child 0–2 years old) were randomly selected for inclusion in the baseline survey sample, stratifying the random selection by pregnancy status. During the baseline interview, information was collected on the last menstrual period date. Women with confirmed pregnancies not enrolled in ante-natal services were referred to village health agents and antenatal services. The baseline survey sample listing included potential replacements to ensure adequate sample sizes were obtained.

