	**Data collection round**		
**Data collected**	**Baseline**	**Mid-line (1.5 years)**	**Endline (3 years)**
*CBCC/village level*			
Village infrastructure and development projects	I		I
CBCC infrastructure and staff	I		I
Parenting/care groups	I		I
Market prices	I	I	I
*Household level*			
Demographics, socioeconomic status	I		I
Expenditures	I	I	I
Agriculture production	I	I	I
*Maternal level*			
Programme exposure	I	I	I
Women's empowerment (Pro-WEAI)		IDI/FGDs	
Role in household decision-making around production and income	I	I	I
Access to productive capital	I	I	I
Access to financial services	I		I
Time allocation	I		I
Group membership	I		I
Physical mobility	I		I
Intrahousehold relationships	I		I
Autonomy in decision-making	I		I
New general self-efficacy scale	I		I
Life satisfaction			
Attitudes about domestic violence	I		I
Maternal depressive symptoms (SRQ)	I	I	I
Height and weight	M	I	M
Haemoglobin (conditional on additional funding)			B
24-h dietary recall	I	I	I
IYCF knowledge and practices	I	I	I
Willingness to pay for specialised foods	I	I	I
*Paternal level*			
Women’s empowerment (Pro-WEAI)	I	IDI/FGDs	I
*Child level*			
Birth information (date, time, mode, place, complications, care, weight)	R	R	
Immunisation and vitamin A	I	I	I
7-day morbidity symptoms, health record (clinic visits, hospitalisations)	I	I	I
Height and weight	M	I	M
Child development (MDAT)	I/O		I/O
Family care indicators	I	I	I
24-h dietary recall			I

*Abbreviations: B*, blood; *CBCC*, community-based childcare centre; *FGD*, focus group discussion; *I*, interview; *IDI*, in-depth interview; *IYCF*, infant and young child feeding; *M*, measurement; *MDAT*, Malawi Development Assessment Tool; *O*, observation; *SRQ*, self-reported questionnaire; *T*, test; *WEAI*, women empowerment in agriculture index

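### The printed ANCOVA needs a baseline MDAT score that children in utero at baseline cannot have, and the section does not say clearly whether that term is in the primary model

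*Protocol article*

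**What the plan says.** The protocol article's Statistical analysis section gives one model for all outcomes: "impact will be assessed using a single difference analysis of covariance (ANCOVA) model with the following form", namely Y_i1 = β0 + β1·T_i + β2·Y_i0 + ε_i. It defines Y_i0 by the words "is the outcome variable at baseline". Later in the paragraph it adds: "Primary analyses will be unadjusted for baseline covariates". It also commits to intention-to-treat and to a main analysis resting on a stated assumption about missing data.

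The primary objective in Table 1 asks for the effect "on child development (motor, language, and cognition) in children (in utero to 2 years of age at baseline), over a 3-year implementation period". Pregnant women are an inclusion group (Study population), and the baseline sample was drawn "stratifying the random selection by pregnancy status" (Recruitment of subjects). Secondary objective 4b is a pre-natal versus post-natal exposure subgroup.

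Table 3 schedules MDAT at baseline and endline only. It schedules the child 24-hour recall at endline only, and haemoglobin (if funded) at endline only.

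**The concern.** A child not yet born at the baseline survey has no baseline MDAT score. The value is undefined by design; it is not an existing value that went unrecorded. The only impact equation in the document therefore cannot be evaluated for a group that the primary objective names and the sampling deliberately includes. A standard regression fit silently omits rows with an empty covariate.

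What is at stake is which effect is estimated. Without these children, the MDAT result would describe children first exposed after birth and would leave out those with the earliest exposure. For child nutrient adequacy and haemoglobin the equation cannot be fitted to anyone, because no baseline measurement is taken.

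**Working it through.** **Step 1: set the texts side by side.**

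- Population for MDAT (Table 1): in utero to 2 years at baseline.
- Measurement (Table 3): MDAT at baseline and endline. A child in utero can contribute only the endline score.
- Model (Statistical analysis): needs both scores for each child.

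The model and the population cannot both hold as written unless a rule is added for Y_i0.

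**Step 2: consider the two readings of the unadjusted primary analysis.**

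- *Y_i0 stays and only further covariates are left out.* ANCOVA is then the primary model, and children without Y_i0 fall out of the fit.
- *Y_i0 also goes.* Every child with an endline MDAT stays, but the primary analysis is then a plain endline comparison. The stated impact model and the efficiency argument for ANCOVA no longer describe it. Any adjusted analysis that uses Y_i0 still meets the same gap.

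**Step 3: try the plan's own precision figure.** Sample size and power gives about 40 clusters per arm, 20 pairs per cluster, ICC 0.02 and a minimum detectable effect of 0.26 SD for MDAT. Alpha and power are not stated; I assume two-sided 0.05 and 80%.

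MDES = (z_α/2 + z_power) × √(2 × [ICC + (1 − ICC)/m] / k)

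= (1.960 + 0.842) × √(2 × [0.02 + 0.98/20] / 40) = 2.802 × √0.00345 = 0.165 SD.

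This is not 0.26. The strictest variant tried at k = 40 and m = 20 (alpha 0.05/12, 90% power) gives 0.244. Since the stated figure does not reproduce from its inputs, I report only ratios, in which alpha, power and k cancel.

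**Step 4: size of the loss.** The in-utero share is not stated, so a range is assumed. Full size is 156 × 20 = 3,120 children. The variance of a between-arm contrast is proportional to 0.02 + 0.98/m.

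| Share in utero (assumed) | m kept per cluster | Children kept | 0.02 + 0.98/m | Variance ratio | MDES ratio |
|---|---|---|---|---|---|
| 0% | 20 | 3,120 | 0.0690 | 1.00 | 1.00 |
| 20% | 16 | 2,496 | 0.0813 | 1.18 | 1.09 |
| 25% | 15 | 2,340 | 0.0853 | 1.24 | 1.11 |
| 40% | 12 | 1,872 | 0.1017 | 1.47 | 1.21 |
| 50% | 10 | 1,560 | 0.1180 | 1.71 | 1.31 |

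A dummy least-squares fit of the printed equation, with Y_i0 undefined for 5 of 20 children per cluster, kept 2,340 of 3,120 rows and none of the in-utero children, as in the 25% row. The ratios assume equal cluster sizes and no attrition, and leave aside any precision gained from Y_i0 itself.

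**Step 5: direction of harm.** Pregnancy status and MDAT scores, aggregated to village level, entered the restricted randomisation, so baseline status was recorded before allocation. Excluding children on that status works the same way in every arm. It narrows the target population and costs precision, but does not bias the comparison between arms.

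**The case against.** The strongest reply is that the equation is only a sketch. It has one treatment dummy for four arms and no cluster term, and the text that follows supplies arm dummies, cluster random effects and district. The section opens by resting causal claims on endline mean comparisons, and it calls the primary analyses unadjusted. The commitments to intention-to-treat and to following up everyone point towards keeping all children. How an absent baseline covariate is coded is ordinary analysis-plan detail, and that plan is not shown.

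Much of this stands. A reader might infer that the protocol excludes in-utero children from the MDAT analysis. It does not say so: the only analysis exclusion it states for enrolled children concerns certain disabilities. Nor is subgroup 4b shown to be impossible, because nothing obliges that analysis to use this exact equation with incomplete rows dropped.

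What does not fall away is the conflict itself. The paragraph adds other terms to the sketch but never says what happens to Y_i0 for unborn children. The remark about unadjusted analyses rescues them only by displacing ANCOVA as the primary model. The missing-data sentence is general and does not address a score that never existed. This is a printed model at odds with a printed population, which goes beyond a detail left to another document.

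**Conclusion.** The concern holds as an inconsistency to be reconciled. As printed, the impact model cannot include part of the primary child-development population, and the text is ambiguous about whether Y_i0 belongs in the primary analysis. If the model were fitted literally, the MDAT effect would refer to post-natal exposure only, the pre-natal side of subgroup 4b would be absent, and the minimum detectable effect would rise by a factor of about 1.09 to 1.31. That range rests on an assumed in-utero share of 20–50% and the stated ICC of 0.02.

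Three stronger conclusions are not supported. There is no between-arm bias, because the exclusion would depend on pre-randomisation status. No absolute detectable effect for this trial should be quoted from these calculations, since the stated 0.26 SD does not reproduce from its inputs. Maternal MPA is unaffected, because women have a baseline dietary recall.

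**What to change.** In the Statistical analysis section, and in the analysis plan if it is silent:

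1. State whether Y_i0 is in the primary model. If it is, say that the unadjusted analysis means no covariates beyond Y_i0. If it is not, describe the primary analysis as an endline comparison and ANCOVA as the adjusted one.
2. Wherever Y_i0 is used for MDAT, keep all index children. Set Y_i0 to a constant (for example 0) for those unborn at baseline and add an indicator for them. The constant does not estimate a missing score; with the indicator it simply gives these children their own intercept. This is sound because the status precedes allocation.
3. Define the indicator by the index child's own status at baseline, not by the woman's pregnancy stratum. The sampling list allows a woman to be pregnant and already have a child under 2, so the stratum may not identify the children without a score.
4. For outcomes with no baseline measurement (child nutrient adequacy, haemoglobin), omit Y_i0.
5. State that no child is excluded for lack of a baseline score.

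The cost is a few sentences and one extra model term, with no new data. It should be settled before treatment allocation is revealed to the analysts.
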